# Intensive 7-day internet-delivered cognitive behaviour therapy for social anxiety disorder: study protocol for a randomised controlled trial

**DOI:** 10.1186/s13063-025-08826-6

**Published:** 2025-04-18

**Keywords:** **S**ocial anxiety disorder, Anxiety disorders, Internet cognitive behavioural therapy, Internet- and mobile-based intervention, Intensive treatment, Cognitive behavioural therapy, Randomised controlled trial

## Abstract

**Background:**

Social anxiety disorder (SAD) is a serious mental health disorder that when left untreated can lead to significant social, occupational, educational, and functional impairment. Cognitive behaviour therapy (CBT) is the recommended first-line psychological treatment for SAD and has been shown to be efficacious in face-to-face and online formats. However, treatment is lengthy, and many people drop out prematurely. Pilot research suggests that brief intensive internet CBT (iCBT) for SAD is feasible and acceptable, but further evaluation using randomised controlled trials (RCT) is needed.

**Methods:**

A RCT to evaluate the acceptability, feasibility, and efficacy of an intensive 7-day iCBT program for adults diagnosed with SAD (with or without comorbid major depressive disorder) in comparison to a waitlist control (WLC) is currently in progress. Eligible participants will be randomised to an intervention or WLC group. Participants allocated to the intervention will complete 6 iCBT modules over 7 days, with CBT skills practice each day, and clinician guidance provided remotely by telephone and email. Participants allocated to the WLC will be given access to the program after a 6-week waiting period. All participants will complete assessments at baseline, 2 weeks and 6 weeks post-baseline. Outcome measures will assess for social anxiety (SIAS, SPS), depression (PHQ-9), personality (LPFS, PID-5-BF), and functioning (WSAS). Intention-to-treat linear mixed model analyses will be used to evaluate primary and secondary outcomes.

**Discussion:**

Previous findings from a pilot trial showed that 7-day iCBT is feasible and acceptable to clients with SAD. Based on these findings, we expect the treatment group will improve significantly on measures of symptoms of social anxiety, depression, and functional impairment compared to the WLC, and these improvements will be sustained at 1-month follow-up. If demonstrated to be effective in this RCT, intensive 7-day iCBT for SAD is a novel way to deliver CBT more quickly, with potential to reach more clients and reduce drop-out rates. It has great potential to provide rapid symptom improvement to individuals with SAD.

**Trial registration:**

This trial was prospectively registered with the Australian New Zealand Clinical Trials Registry on March 1, 2022 (ACTRN12622000361707).

**Supplementary Information:**

The online version contains supplementary material available at 10.1186/s13063-025-08826-6.

## Background

Social anxiety disorder (SAD) is a highly prevalent and often debilitating condition in which social interactions or being observed triggers intense fear or anxiety about being negatively evaluated or rejected by others [1]. SAD is estimated to impact approximately 14.4% of Australians between the ages of 18–85 over a 12-month period [2] and has been found to be more prevalent in women, particularly during adolescence [1]. Left untreated, SAD can lead to significant social, occupational, educational, and functional impairment for the individual [3], as well as social and economic impacts on wider society [4]. SAD has been found to be highly comorbid with other mental health conditions, particularly major depressive disorder (MDD), which SAD often precedes [5], and personality disorders, with co-occurrence of SAD and avoidant personality disorder estimated to range from 22 to 89% [6–8]. Notably, both comorbid depressive symptoms [9] and personality pathology [10] can exacerbate the severity of social anxiety symptoms and impact treatment response.

Clinical practice guidelines recommend cognitive behaviour therapy (CBT) as the preferred first-line treatment for SAD [11]. CBT has been shown to be efficacious when delivered in both face-to-face and online formats [11], with some studies finding that internet CBT (iCBT) is just as, if not marginally more, effective than face-to-face CBT, as well as more accessible [12, 13]. A systematic review [14] of over 20 randomised controlled trials (RCTs) found that iCBT (when delivered over 9 or 10 weeks) had a moderate positive average pooled between-group effect size (*g* = − 0.55) on patients’ social anxiety symptoms relative to control groups, increasing to a large pooled between-group effect size (*g* = − 0.79) when compared to a waitlist control group. Treating social anxiety symptoms using iCBT has also been found to have positive effects for treating comorbid MDD and depressive symptoms [15, 16].

Despite its efficacy, CBT for SAD is relatively lengthy, with a typical duration of 8–15 sessions over 10–16 weeks, and there are high drop-rates (an average of 18.3% for individuals with SAD; [17]). This means that many participants do not receive a full ‘dose’ of treatment and are at risk of poorer treatment outcomes [18, 19]. To address issues with treatment retention, CBT has been adapted to be successfully delivered in shorter or more intensive formats, in concentrated face-to-face sessions over 1–4 weeks, or in longer, more intensive sessions over 1–2 days. Promising effects for intensive CBT have been found for the treatment of perinatal anxiety [20], panic disorder [21, 22], and insomnia [23] in both face-to-face and iCBT modalities. Further meta-analyses have also found that intensive CBT and standard paced face-to-face CBT results in equivalent outcomes for anxiety and obsessive–compulsive symptoms, and may lead to greater improvement in depressive symptoms.

Some research studies have also found that intensive CBT can effectively treat SAD in a face-to-face, group-based format [24–28]. To the best of our knowledge, until our team conducted a pilot trial of intensive internet CBT, no studies had evaluated the efficacy of intensive CBT for SAD when delivered online and individually. Delivering intensive CBT treatment online individually may help overcome several barriers to accessing face-to-face treatment, including travel time, cost, appointment wait times, stigma, and clinician availability [29, 30], as well as the potential anxiety triggered by face-to-face contact with a clinician or a group-based setting [31]. The shorter lead time of an intensive treatment also means it has the potential to produce more rapid improvement in both symptoms [32] and functioning [33], which is often significantly impaired in people with SAD.

### 7-day iCBT for social anxiety disorder

We developed a novel intensive iCBT intervention for SAD, adapted from an existing evidence-based 6-module iCBT program for SAD. The program is typically delivered over 10–12 weeks [34–44] and available on www.thiswayup.org.au to individuals residing in Australia. The intensive delivery of the program was modelled on another pilot trial of an intensive exposure-based iCBT program for panic disorder and agoraphobia [45]. The 6 modules are delivered over a 1-week period (one module completed per day, with a rest day on day 6), and support is provided by a psychologist via telephone and email throughout the treatment week. Modules are approximately 20–30 min in length, and participants are encouraged to spend 3–4 h per day practising the assigned skills. For a description of the contents of the intervention see Table 1. The results of a small pilot trial conducted in 2020 with 16 participants with SAD [33] provided preliminary evidence of the intervention’s acceptability and feasibility, showing it significantly reduced participants’ social anxiety symptoms (Hedges’ *g*_*s*_ = 1.26–1.9), functional impairment (*g*_*s*_ = 0.88–0.98), and comorbid depressive symptoms (*g*_*s*_ = 0.88–0.98). The trial showed strong retention with 93.8% (15 out of 16) participants completing all modules; all participants rated the program as either very or mostly satisfactory.

**Table 1 Tab1:** Intensive internet-based cognitive behaviour therapy for social anxiety disorder program overview

Module	Title	Description	Overview	Homework tasks	Follow-up
1	Social anxiety explained	Learn about how social anxiety affects you and how it can be treated	• Psychoeducation about social anxiety, CBT, and the ‘anxiety cycle’ • Setting goals for the program • Psychoeducation about the fight-or-flight response and arousal reduction strategies (e.g. controlled breathing, progressive muscle relaxation, physical exercise)	• Goal setting for the course • 30 min of exercise a day, 3 days per week • Practising controlled breathing 2–3 times per day • Completing guided progressive muscle relaxation	Day 1 telephone check-in call
2	Tackling avoidance	Understand how avoidance keeps anxiety going and how anxiety can be overcome using exposure therapy	• Psychoeducation about the role of avoidance and safety behaviours • Identifying one’s own avoidance and safety behaviours • Rationale for exposure therapy • Creating an exposure step ladder	• Identifying avoidance and safety behaviours • Creating an exposure step ladder • Confronting situation at the bottom of step ladder to begin with, then slowly moving up • Continuing with exercise, controlled breathing, and progressive muscle relaxation	
3	Trouble-shooting exposure	Review how exposure therapy is progressing and learn how to do behavioural experiments	• Reviewing and trouble-shooting exposure tasks • Using video feedback to test anxious predictions	• Identifying any pitfalls experienced with exposure • Selecting and implementing a solution for these pitfalls • Continuing to progress through exposure step ladder • Continuing with exercise, controlled breathing, and progressive muscle relaxation	Day 3 telephone check-in call
4	Unhelpful thinking styles	Learn to identify unhelpful thinking styles	• Introduction to the cognitive model and unhelpful thinking styles • Thought monitoring • Attention shifting	• Identifying relevant unhelpful thinking styles • Identifying times when worry is most prominent • Practising thought monitoring • Practising attention shifting • Continuing to progress through exposure step ladder • Continuing with exercise, controlled breathing, and progressive muscle relaxation	
5	Thought challenging and social skills	Challenge unhelpful thinking styles and learn about social skills	• Steps for thought challenging • Strategies for improving communication skills	• Practising thought challenging • Reading extra resources on conversation skills and assertiveness • Continuing to practise attention shifting • Continuing to progress through exposure step ladder • Continuing with exercise, controlled breathing, and progressive muscle relaxation	Day 5 telephone check-in call (optional)
6	Preventing relapse	Summarising the course and preventing relapses	• Psychoeducation about lapses and relapses • Relapse prevention planning • Identifying where to seek further support (if required)	• Continuing with program skills • Complete relapse prevention plan	

Despite these encouraging initial findings, further investigation is needed to evaluate the program’s efficacy. Because of the lack of control group in the pilot trial, it is unknown whether the improvements observed were attributable to the treatment or to another factor, such as the passage of time or repeated assessments. Further, the study relied on self-report measures of social anxiety. The lack of follow-up assessment also means it is unknown whether the gains observed were maintained over the longer term. A RCT with a larger sample, comparison to a control group, and inclusion of follow-up and clinician-rated assessment is now needed to evaluate the efficacy of the program.

A further important area of investigation is for whom intensive iCBT is best suited. While an intensive online format has potential for rapid symptom improvement, unwanted side effects (e.g. feeling overwhelmed from time pressure) have been reported by some participants in intensive iCBT (e.g. [20, 21, 33]), so better understanding of which patients may benefit most from this new treatment format is important. One study [46] of standard-paced iCBT for SAD for example found that older age and female gender predicted better treatment adherence and outcome, while another [47] found lower baseline severity predicted better post-treatment outcomes. A meta-analysis of 28 studies of standard-paced CBT for SAD however found no consistent evidence for strong pre-treatment predictors of response across the studies [48]. It is also unclear whether the efficacy of intensive iCBT is impacted by common comorbidities in SAD, such as depressive symptoms and personality pathology, which have been shown to predict poorer treatment response in standard-paced CBT [48, 49]. We therefore sought to investigate these questions further by examining predictors of treatment response and adherence to intensive iCBT for SAD, including demographic characteristics (age, gender) and comorbid psychopathology (baseline severity of depression and SAD symptoms, personality pathology).

### The current study

The proposed research will examine whether delivering iCBT in an intensive format over 1 week is effective in treating SAD symptoms relative to a waitlist control (WLC) group. A WLC condition was chosen as a comparator for several reasons. First, it provided a practical and feasible first step in evaluating the efficacy of this treatment, to determine whether a larger, more costly trial to compare it to an active treatment group or standard-paced CBT is warranted. WLC provided a clearer measure of treatment effects as it is more standardised than a usual care control group. Usual care control groups introduce more heterogeneity because participants receive varying levels and types of treatment. The WLC design also controlled for some factors such as the passage of time, the effects of repeated assessment, and regression to the mean which may have explained some improvements observed in the previous pilot trial. This study is the first RCT evaluating the efficacy of intensive, individual, online CBT for SAD. It is strengthened by the addition of follow-up assessment 1 month post-treatment and a clinician-rated diagnostic interview to assess the efficacy of the treatment beyond the self-report measures used in the pilot trial.

### Trial aims and hypotheses

This protocol has been reported according to SPIRIT guidelines for reporting of trial protocols [50, 51]. The primary aim of this study is to investigate the efficacy of the intensive iCBT for SAD program [44] in improving symptoms of social anxiety at post-treatment and 6-week follow-up, relative to a WLC group. The secondary objectives of the trial are to evaluate the efficacy of the program in reducing symptoms of depression and functional impairment/quality of life at post-treatment and follow-up. A third aim is to further explore the program’s acceptability and feasibility. We aimed to test whether the strong adherence and satisfaction observed in the pilot trial were replicated in a larger sample and outside of the COVID-19 pandemic context. A fourth aim is to explore predictors of treatment effectiveness, including participant age, gender, baseline symptom severity, and personality.

The primary hypothesis is that participants who receive the intensive iCBT for SAD intervention will show significantly reduced social anxiety symptom severity compared to the WLC group. We also hypothesise that intensive iCBT for SAD will be significantly more effective at improving participants’ comorbid depressive symptoms and increasing quality of life relative to the WLC group. The third hypothesis being tested is that intensive iCBT for SAD will be acceptable to participants according to high adherence (> 80%) and treatment satisfaction ratings. A further set of exploratory analyses will investigate whether the effectiveness of the intervention is predicted by participant age, baseline symptom severity, and personality functioning.

## Methods

### Trial design and setting

This superiority trial will utilise a two-arm, parallel group RCT design with an equal allocation ratio. Outcome measures will be assessed at baseline, post-intervention (primary endpoint, measured at 2 weeks post-baseline), and follow-up (secondary endpoint, measured at 6 weeks post-baseline). The primary time point of interest is post-treatment (2 weeks post-baseline). A 6-week follow-up was selected to ensure participants in the control condition were provided with the intervention after a reasonable duration and to reduce participant attrition.

This clinical trial is sponsored by the University of New South Wales (UNSW) and ethics approval has been granted by the UNSW Human Research Ethics Committee (HREC; HC#220,089). The trial has been registered with the Australian New Zealand Clinical Trials Registry on March 1, 2022 (ACTRN12622000361707).

### Eligibility criteria

Inclusion criteria includes adults aged 18 years or over, residing in Australia, fluency in written and spoken English, access to a computer and the internet, elevated scores on both the Social Interaction Anxiety Scale [> 34; SIAS, [52]] and the Social Phobia Scale [> 24; SPS, [52]], meeting DSM-5 diagnostic criteria for SAD according to a telephone diagnostic interview, willingness to provide basic demographic information and their general practitioner’s (GP) contact details, and on a stable dose of medications if applicable (no new medications or changes to existing medications in the 2 months prior to applying for the study).

Exclusion criteria are as follows: self-disclosed pre-existing diagnosis of schizophrenia, psychosis or bipolar disorder, daily or nearly daily suicidal ideation (score of ‘3’ on item 9 of the Patient Health Questionnaire-9 [PHQ-9; [53]]), or recent suicidality as determined by clinician interview (i.e. current suicidal intent, self-harm, or suicide attempts in the past 5 years), very severe depression (PHQ-9 scores of ‘24’ or above), currently receiving CBT, or commenced or changed mental health medication in the 2 months prior to application.

### Trial recruitment processes

The trial procedure and enrolment process is outlined in Fig. 1. This study is utilising an online recruitment strategy, with self-selecting participants recruited through paid study advertisements published on the Black Dog Institute website and social media channels (Facebook, Twitter, and Instagram), and through a research register of people with social anxiety who have consented to being contacted about research study participation. Applicants will be directed to the study website, where they can read information about the study, and click on a link to read the participant information statement and consent form (PISCF), administered by REDCap survey platform [54, 55]. To register, individuals provide electronic informed consent and are emailed a copy of the PISCF. Each time a participant logs in to the website to complete a lesson and/or questionnaire, this will be taken as a sign of continued consent to participate.

**Fig. 1 Fig1:**
[figure not shown]
Consolidated Standards of Reporting Trials (CONSORT) participant flowchart illustrating enrolment and study procedure

Applicants are next directed to complete an online screening and eligibility questionnaire, including demographic information, GP details, eligibility questions, and the SIAS, SPS, and PHQ-9. Ineligible applicants will be redirected on-screen and by email to further support services including digital mental health treatment options (e.g. the standard-paced version of the treatment through THIS WAY UP under supervision of their GP) and crisis support lines, and encouraged to speak with their GP about alterative support.

Eligible applicants will proceed to a phone call with one of the study clinicians (either a provisional psychologist, registered psychologist, or clinical psychologist) to complete additional eligibility questions, an abbreviated version of the Anxiety Disorders Interview Schedule for DSM-5 [ADIS; [56]] Social Anxiety Disorder and Major Depressive Disorder modules, and a comprehensive risk assessment.

Participants who meet inclusion criteria will be randomly allocated to one of two treatment groups (see randomisation and allocation procedures below) and verbally informed of their treatment group allocation and next steps. Participants’ general practitioners will be informed by letter of their participation and an outline of the intervention content.

Participants can self-withdraw their consent to take part in the study at any time by emailing the research team or submitting the UNSW standard withdrawal form, appended to the PISCF. Participants may also be withdrawn from the study if they experience a serious adverse event that is either attributable to the study intervention or procedure or that means they can no longer participate in the study.

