### Safety monitoring and management

This trial will follow a standardised risk management protocol based on previous clinical trials of digital mental health interventions run by the research team and use a Trial Management Group (TMG) to supervise the overall conduct and safety of the trial. This is in accordance with the National Health and Medical Research Council (NHMRC) guidelines on Data Safety Monitoring [57], which state that a TMG is an appropriate alternative to a Data Safety Monitoring Group for non-commercial trials. All adverse events and serious adverse events will be formally recorded and reported to the TMG, and in a report and to the UNSW HREC by the chief investigator. The TMG may recommend pausing or ending the trial due to participant safety concerns. UNSW can audit trial conduct at any time, and this process will be independent of the investigators.

To ensure the safety and wellbeing of participants, several methods are incorporated into the study design. First, all applicants will complete measures of suicidal ideation and depression symptom severity (i.e. PHQ-9). Second, eligible applicants will also complete a comprehensive phone-based risk assessment with a study clinician during the enrolment telephone interview. Any applicant who has recent history of self-harm, active suicidal intent, or recent suicide attempts will be ineligible for the study, and complete a phone-based safety plan, and provided referrals to alternative sources of crisis and ongoing support. Any applicant or participant who endorses suicidal ideation (without current intent) will complete a collaborative phone-based safety plan prior to their initial or ongoing participation; this safety plan will be emailed to them. If needed, further support services accessible after the study will also be discussed with participants. Participants will be emailed crisis support options in their orientation email, instructed to monitor for mood changes during trial participation, and contact the research team or their GP during business hours for non-emergencies, or call the state-wide crisis support teams or emergency numbers if in crisis.

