Third, all participants will be actively monitored for mood deterioration, increase in suicide risk, or the experience of adverse side effects of the intervention in their questionnaire responses (PHQ-9, pre-module questions), during clinician check-in calls, and during the follow-up questionnaires and interview. Automated alert emails will be sent to the trial coordinator if participants score greater than ‘1’ on item 9 of the PHQ-9 at any time during the trial, indicating experience of suicidal thoughts several times over the past 2 weeks, and participants will be contacted by a study clinician the same or next business day to check in and complete a risk assessment and safety plan as needed. Participants will be provided the option to withdraw from the study if it is causing distress and referral options for a higher step of care will be discussed. Any presence of risk or changes in applicant or participant risk profile will be discussed amongst the TMG during weekly meetings and documented in the trial safety monitoring register.

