### Control: waitlist control group

Participants allocated to the WLC group will be informed that they will be able to access the treatment after a waiting period of 6 weeks, during which they will complete three sets of online questionnaires. WLC participants will be sent automated emails via the REDCap platform with a link to complete questionnaires the day after their interview is completed (baseline, T1), 2 weeks later (T2), and 6 weeks post-baseline (T3). At T3, they will also be contacted to re-complete the telephone diagnostic interview, after which they will schedule the start date for their treatment week if they still choose to participate. WLC participants will follow the same procedure as the treatment group before (preparation call), and during their treatment week, receiving the treatment and clinician support over 1 week, and complete post-treatment questionnaires 1 week after completing their intervention. This post-treatment assessment will be used to assess WLC participants’ immediate treatment outcomes which will be included in the analysis of predictors of treatment outcome. The WLC will not be asked to complete any further follow-up assessments to minimise participant burden.

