### Statistical analysis

All analyses will be undertaken using intention-to-treat approach. Linear mixed models, with a random intercept for subject will be used to analyse primary and secondary outcomes, and covariances matrixes used to assess relationships between variables. This approach will be used to manage missing data and account for correlation between repeated measures. Before conducting the analyses, patterns of missing data will be assessed through data visualisation, and Little’s Missing Completely at Random (MCAR) test to determine whether the data are missing at random. If there are significant group differences (as determined by independent samples *t*-tests) in the amount of time elapsed between the intake interview and completion of baseline measures, this variable will be included as a covariate in the linear mixed models. Planned contrasts will be used to compare pre- and post-treatment, and pre-treatment and 1-month follow-up, and planned pairwise comparisons will be used to compare between-groups at post-treatment and follow-up. To control for the risk of type 1 error with a co-primary outcome, the alpha level for significance will be adjusted using a Bonferroni correction (alpha set at 0.025 to determine statistical significance for the SIAS and SPS co-primary outcome measures). Linear mixed models will be utilised to test the predictors of treatment outcome. Within- and between-group effect sizes will be calculated using Hedges’ *g* (with 95% confidence intervals) to estimate the within-group changes from baseline to post-treatment, and baseline to follow-up, and between-group differences on primary and secondary outcome measures at post-treatment and follow-up.

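### The team may withdraw a participant from the study, not only from the programme, after an intervention-related serious adverse event, so primary-endpoint scores can be lost in the iCBT arm alone for a reason tied to harm

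*Protocol article*

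**What the plan says.** Trial recruitment processes first covers the participant's own withdrawal of consent. It then gives a separate rule for the team: "Participants may also be withdrawn from the study if they experience a serious adverse event that is either attributable to the study intervention". The same sentence extends this to events caused by trial procedures and to any such event, whatever its cause, that rules out further participation. Safety monitoring and management adds an option that belongs to the participant: "Participants will be provided the option to withdraw from the study if it is causing distress". Both provisions refer to the study as a whole.

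The same safety section keeps the event itself on record: "All adverse events and serious adverse events will be formally recorded and reported to the TMG". It also has participants monitored through the PHQ-9, the check-in calls, the follow-up questionnaires and the follow-up interview.

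On exposure, the waitlist section says that controls are told "they will be able to access the treatment after a waiting period of 6 weeks". They complete the 6-week assessment (T3) before scheduling their treatment week.

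On analysis, the article states: "All analyses will be undertaken using intention-to-treat approach". The models are linear mixed models with a random intercept for subject, and of these it says: "This approach will be used to manage missing data and account for correlation between repeated measures". The primary time point is T2, 2 weeks after baseline (Trial design and setting).

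**The concern.** Stopping a treatment and leaving a trial are different events. An intention-to-treat comparison is best served when someone who stops treatment is still asked for outcomes. Here, a rule triggered by harm from the programme can end both at once, on the team's initiative, for a person who has not withdrawn consent. The team judging attribution knows the allocation (Blinding).

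Two things are at stake. The first is the between-group effect at T2: if participants who did badly on iCBT leave before T2, the arm is represented by those who did better. The second is safety information after the event: the side-effect questions at T2, the PHQ-9 with its item 9 alerts, and the T3 interview. The article itself notes that unwanted effects have been reported with intensive iCBT and makes acceptability an aim, so the trial needs these data.

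**Working it through.** **1. Which arm can the rule reach before T3?** Setting the rule against the exposure schedule:

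- Event attributable to the intervention: iCBT arm only, because controls have not had the programme.
- Event attributable to a study procedure: either arm, because both complete questionnaires and interviews.
- Event of any cause that prevents participation: either arm.

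One of the three limbs is therefore one-sided within the randomised comparison.

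**2. What would the model have to work with?** iCBT participants complete baseline (T1) just before module 1, and the SIAS and SPS were also taken at recruitment (T0). Someone withdrawn during the treatment week has only pre-treatment scores. For that person the random-intercept model takes the post-treatment change from the retained iCBT participants. That is valid if, given the observed scores, those lost would have changed as those retained did. A withdrawal caused by harm that no observed score captures makes this doubtful. Little's test, which the article plans, cannot settle it: it examines whether missingness is related to observed values, not to the unseen ones. A withdrawal between T2 and T3 leaves the primary endpoint intact and affects only T3.

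**3. The plan's own sample size.** Inputs from Sample size calculations: effect 0.92, alpha 0.05 (two-sided assumed), power 0.80.

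- Normal approximation: n = 2 × (1.960 + 0.842)² / 0.92² = 18.6, so 19 per group.
- Noncentral t: 20 per group, power 0.809.
- Attrition: 20 / (1 − 0.20) = 25 per group.

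The stated 20 and 25 reproduce, so no figure in the article is in error on this point.

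**4. Possible size of the distortion.** Let k of the 25 iCBT participants be lost before T2. Let h be their true standardised effect against the waitlist mean, which is the same scale as the 0.92, and let those retained have 0.92. Neither k nor h is in the documents; both are assumptions. The model is taken to make no correction.

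Effect in all 25 = [(25 − k) × 0.92 + k × h] / 25

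Overstatement = (k / 25) × (0.92 − h)

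| k | h | Effect in all 25 | Overstatement | Relative to the effect in all 25 |
|---|---|---|---|---|
| 1 | 0 | 0.883 | 0.037 | 4.2% |
| 1 | −1 | 0.843 | 0.077 | 9.1% |
| 2 | 0 | 0.846 | 0.074 | 8.7% |
| 2 | −1 | 0.766 | 0.154 | 20.0% |

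Example for the last row: (23 × 0.92 − 2) / 25 = 19.16 / 25 = 0.766, and 0.92 − 0.766 = 0.154. Each loss also uses one of the 5 places per arm allowed for attrition.

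**The case against.** The strongest reply is that this is a condensed article. What happens to data after withdrawal may be set out in the full protocol, the consent form, the university's withdrawal form or the standardised risk management protocol, none of which is shown. That limits confidence about what was done. It does not remove the point, because the article states a rule at study level; it is not merely silent.

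Several stronger readings are tempting, and the documents do not support them:

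- *That data were lost.* The rule is discretionary and the article reports no such case. In the pilot, 15 of 16 participants completed all modules, and higher-risk applicants are excluded at entry, so such events may be few or none.
- *That loss would be confined to the iCBT arm.* Only the intervention-attributable limb is one-sided.
- *That harms would go unrecorded.* All adverse events are to be recorded and reported. Only later scheduled assessments are at risk.
- *That the rule contradicts the intention-to-treat statement.* The analysis section expects missing scores and plans for them. The two passages are in tension, because the expected mechanism may not be missing at random, but neither makes the other impossible.
- *That study withdrawal is the only response to distress.* The safety section also provides for prompt contact, risk assessment, safety planning and discussion of referral, and withdrawal for distress is the participant's choice. Adherence is counted as modules completed out of 6, so partial completion need not mean leaving the study.

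It is also fair to say that the number harmed and the extent of their worsening are assumed. The table shows what a few losses could do and does not estimate what happened.

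**Conclusion.** The point holds in a limited form. The article gives the team a discretionary power to withdraw people from the study after a serious adverse event. Before T3, one limb of that power can act only on the iCBT arm. If it was used before T2, the primary outcome and later scheduled safety data could be missing in one arm for a reason related to harm, and the planned model could not be relied on to correct for it. With one or two such losses among 25, the overstatement would be about 0.04 to 0.15 on a planned effect of 0.92. This assumes a true effect of 0 to −1 SD in those lost and no correction by the model. If no one was withdrawn under this limb before T2, the effect on the primary result is nil. The point deserves correction but does not by itself undermine the trial.

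**What to change.** **Wording, for a corrected protocol or a further study.** Reconcile Trial recruitment processes, Safety monitoring and management and Statistical analysis by defining two separate events: stopping the programme, and withdrawing from data collection. State that outcome and safety assessments continue to be sought after the first, unless the participant withdraws consent to them or cannot take part. Clinical decisions about the modules stay where they are now. The cost is a few sentences in the protocol and withdrawal form and, in a further study, some additional reminder contacts.

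**This trial.** Trial status says that data collection was finalised by the end of July 2024, so what remains is analysis and reporting:

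- Keep all randomised participants in the intention-to-treat set.
- Report programme stops and study withdrawals separately, by arm, timing (before T2, or between T2 and T3) and reason.
- If any harm-related withdrawal occurred before T2, add a sensitivity analysis of the SIAS and SPS that assumes unfavourable T2 outcomes for those participants, for example over the 0 to −1 SD range used above. If there was none, say so in one line.

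This needs no new data, only the withdrawal records and, at most, one extra analysis for each co-primary outcome.
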